|  | **The innovation provided by AEVE are:**  -a) The nonprofessional volunteers become experts of his child and their energy and enthusiasm from week to week are a precious asset to make the child "come into our world", under the control of the professional psychologist; the evaluation grids (file AEVE1 DEC1 PJ3) make it possible to gather observations of each participant and to obtain a faithful and precise image of the evolution of the child and, consequently, progress.  - b) No imposition of rhythm exceeding the child's endurance. If the child needs to rest, he is offered a quiet game or is allowed to sleep. When crises appear (dissatisfaction, incomprehension, frustration) the volunteer remains calm, attempts to verbalize the cause of the crisis - if he guessed it - and settles an activity to which the child ends up interested  - c) AEVE considers it is possible to bring the child to the end of the method of the 3I to a level of autonomy and capacity of learning, allowing a real inclusion in the school. This is most often prepared by home school in phase 3. And such access to school is much more beneficial for the child (and for his class).  - d) The 3I method is obviously not a panacea or a miracle method, but it can be adapted to many cases because of the flexibility of its implementation. |

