| 2.4 | **Description and justification of the methods of use of the device and the duration of treatment:**  The playroom layout is designed to reduce the child's sensory perception: the light is diffused, the floor is soft, the sounds are damped, the games are stored on high shelves and the floor is is not cluttered with objects. A mirror on the wall, a swing are part of the basic equipment.  The volunteers follow each other in increments of one hour and a half (two in the morning, two or three in the afternoon). In phases 2 and 3, the child progressively left the playroom for external contacts, then for pre-school learning.  Additional care, is useful (speech therapy, psychomotricity or others) as they do not present learning modes contrary to the developmental approach 3I. Thus, assisted communication tools such as PECS are, in most cases, not recommended in the context of additional support. Likewise, learnings based on reinforcers other than mere verbal encouragement are not recommended.  The duration of 3I method usually lasts from two to three years. If the child starts from a relatively favorable level of development, it is possible (on average almost two out of ten according to the retrospective study of 120 children) that the child is admitted to class before the end of two years of care. |
| 2.5 | The research will be conducted according to the protocol with data record prior the beginning of the trial will be used for the purposes of the longitudinal study as soon as the parents have given explicit informed consent. |
| 2.6 | **Description of the population to study:**  An experimental group of 20 children with a diagnosis of Autism Spectrum Disorder who are not in school and benefiting from the 3I method between 30 and 35 hours per week will be recruited (Method 3I 'pure', without further intervention). The age of onset of care will range from approximately 2 to 12 years. Older children may be studied as well and may be the subject of separate studies. |

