| **5.1** | **Inclusion criteria**  **•** Child and adolescent diagnosed with ASD (criteria: ADI-R and CARS)  • Parental agreement and signed informed consent  • Child who starts the 3I method from January 2013  • Age between 2 years and 12 years at the beginning of the treatment 3I for the experimental group  • Consistent application of the method (adequate playroom, number of volunteers and number of hours of stimulation between 30-35h per week)  • Out-of-school child and adolescent who benefits from the 3I 'pure' method, without any other major intervention.  • Child with French in mother tongue |
| **5.2** | **Criteria of non-inclusion**  • Associated pathology (epilepsy, Rett syndrome ...)  • Child with Asperger syndrome  • Family situation that does not make it possible to consider taking care of 3I in the long term  • Children who do not do 100% of 3I method (part-time support)  • Child receiving other type ABA care, TEACCH |
| **5.3** | **Premature stop procedure:**  The regulation concerning the events and undesirable effects will be respected.  In the event of an undesirable effect (lasting aggravation of behavioral disorders)  In the case of significant improvement indicating partial or total re-enrollment  In case of unilateral decision of the family to leave the research and / or care 3I  In the first two cases, the investigator and the collaborating investigator, possibly solicited by a referent psychologist of the child, will decide on the premature exit of the study, having, as far as possible, carried out the tests so to limit the missing data (and also in the third case). |
| **6** | **Treatment other than the device:**  Additional interventions in speech therapy, psychomotricity, occupational therapy and other interventions that may require technical actions that are not the responsibility of 3I volunteers may be associated. These interventions will be recorded to analyze if they can biased the interpretation of the results. |
| **7** | **Performance evaluation:** |
| **7.1** | **Description of performance evaluation parameters:**  • The severity of autistic disorders (CARS)  • Homogeneity of development (PEP)  • The development of socio-communicative skills (IMITATION)  • Adaptive behavior (VABS) |

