| **8** | **Security assessment**  The 3I method is carried out in a family setting, with the exception of the center of Lud'éveil Courbevoie for five children. Child safety is ensured mainly by his parents. The equipment in the playroom provides a camera through which all sessions can be viewed.  The risk of exposure to pedophilia by volunteers is not to be neglected; it is lessened by the presence of another person in the immediate vicinity of the playroom, and by the recording of the camera, which any interruption would raise the mistrust of the parents.  The occurrence of any events or adverse effects, within the meaning of § 5.3 will be notified by the 3I psychologist assigned to the child to the investigator. |
| **9** | **Statistisques :** |
| **9.1** | **Description of planned statistical methods and timing of interim analyzes:**  Statistical methods: It will compare the mean of the scores or the ages of developments of the cohort obtained with the different tests of the evaluation carried out at T0, T1, T2. Once the conditions of application of the parametric tests are verified we will apply a general linear mixed model (GLMM) to obtain a better statistical power while taking into account the individual variations of the subjects (subject effect). Additional analyzes will take into account the age group of the child in covariate, as well as the severity of the disorders, and the level of language (evaluated at Vineland). Individual studies may be carried out.  Independent variable:  • Time: evaluation at T0, T1, T2  Dependent variables for each test:  • CARS: total score  • VABS: age of development by domain (4)  • PEP-R: overall development age, age of development by domain (7) IMITATION: score by domain (3), number of socio-emotional behavior (positive vs negative)  In addition, we will analyze the profiles of each subject to evaluate areas of evolution (case study).  Calendar of interim analyzes:  • Intermediate analysis on T1 tests compared to T0  • Final analysis on T2 tests compared to T0 |
| **9.2** | **Expected number of subjects to include and statistical justification:**  About 20 subjects in the experimental group 2 years-12 years to perform parametric tests. |
| **9.3** | **Degree of signification:**  The main effects and interactions will be considered significant if the p-value is lower than the risk α = 0.05 |

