| **9.4** | **Statistical criteria for stopping the search:**  If the interim analysis at T1 showed a significant deterioration of the measures of functioning of the children |
| **9.5** | **Method of taking into account missing data:**  • To take into account the missing data we will use alternative sources of information. For example, in the case where the child does not realize an item (for lack of interest) this information will be collected from the child's parents or psychologists. This information should be verified on written accounts of volunteers or video recordings of play sessions. If there is missing data in one of the tests, the subject data concerning the test in question will be excluded from the analysis.  • In the case of premature termination of the method (unilateral decision of the family) tests will be made to estimate the evolution of the child, even outside the scheduled timing for assessments. If it is impossible to carry out these tests, we will be able to use the last films of the working sessions to rate CARS and Vineland. In all cases, those lost to follow-up will have to be taken into account in the interpretation of the results because they could constitute a bias (children progressing insufficiently being more likely to stop care prematurely). |
| **9.6** | **Change management at the initial statistical level**  A priori not applicable |
| **10** | **Right of access to data and source documents**  The right of access to the data and source documents will be strictly reserved to the investigator, to the collaborator of the investigator and to the person in charge of the quality control (cf §11) |
| **11** | **Quality control and quality assurance**  The investigator's collaborator will work under the control of the investigator. The relatively repetitive nature of the tests performed did not seem to require the intervention of a third party in quality control and quality assurance. |

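### Section 5.3 allows a child to leave the study for improving enough to return to school, keeps no month-24 assessment for that child, and gives no rule for the exit test

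*Protocol*

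**What the plan says.** - **Exit ground (Protocol 5.3).** The premature-stop list has three cases: an undesirable effect, "In the case of significant improvement indicating partial or total re-enrollment", and a family's own decision. In the first two, the investigator and the collaborating investigator "will decide on the premature exit of the study, having, as far as possible, carried out the tests so to limit the missing data". The request for tests at exit also covers the third case.
- **Aim of the method (section 2, AEVE's innovations, point c).** The child is to be brought "to a level of autonomy and capacity of learning, allowing a real inclusion in the school".
- **Expected frequency (2.4).** Admission to class before two years of care is put at "on average almost two out of ten according to the retrospective study of 120 children". The sentence opens with children whose starting level is relatively favourable.
- **Schedule and analysis (4.2, 9.1, 9.2).** T0 is at month 1 of care, T1 at month 12 and T2 at month 24. The closing comparison is "Final analysis on T2 tests compared to T0", using a mixed model. The size is "About 20 subjects in the experimental group 2 years-12 years to perform parametric tests".
- **Missing data (9.5).** The rule reads "If there is missing data in one of the tests, the subject data concerning the test in question will be excluded from the analysis". Off-schedule testing, and rating from films, are described for a family's unilateral decision. The one bias named is "children progressing insufficiently being more likely to stop care prematurely".

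**The concern.** Reaching school is what the method is for, and 5.3 makes the same event a ground for leaving the study. The decision rests on the child's observed improvement, and 4.8 declares blinding not applicable, so whether a scheduled T2 value exists can depend on the outcome being measured.

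The other sections do not repair this. No visit at month 24 is provided after such an exit. An exit test is taken at the exit date, and 9.1 does not say whether it counts as T2, as an extra time point, or not at all. Under 9.5 the child's data for a test with a missing value may be dropped, and the anticipated bias is only the opposite one.

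At stake is the final T2 versus T0 contrast. There is no control group, and 4.4 relies on comparison with published data, so it matters which children the T2 mean describes. A later analysis plan can choose a model, but it cannot recover month-24 assessments that were never made.

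**Working it through.** The protocol gives no effect size, SD, power or dropout rate behind its 20 subjects, so there is no figure of its own to reproduce. The steps below size the problem. Items marked (A) are assumptions.

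**1. How many exits.**
- If two in ten applies to all children: 20 × 0.2 = 4 exits, 16 remaining. P(at least one) = 1 − 0.8^20 = 0.99. By the binomial, P(at least two) = 0.93 and P(at least four) = 0.59.
- If the rate is half that (A): 20 × 0.1 = 2 exits. P(at least one) = 1 − 0.9^20 = 0.88.
- The denominator in 2.4 is ambiguous, so 4 is an assumption. On the other hand, 5.3 is also triggered by partial re-enrolment.

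**2. Exits excluded from T2.** The gain T2 − T0 is taken as normal, in SD units of the gain, with true mean 0.70 (A). The 4 of 20 children highest on an exit score leave, and that score has correlation ρ with the gain (A).

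The large-sample shift in the mean for the remaining 80% is −ρ·φ(c)/0.8, with c = z(0.80) = 0.842 and φ(c) = 0.280. So φ(c)/0.8 = 0.35, and the shift is −0.35ρ: 0, −0.105, −0.175 and −0.245 SD for ρ = 0, 0.3, 0.5 and 0.7. Simulation with exactly 4 of 20 removed (40,000 runs, two-sided 0.05, one-sample t on the gain) agrees:

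| ρ | mean gain, 16 remaining | power |
|---|---|---|
| no exits (n = 20) | 0.70 | 84% |
| 0 | 0.70 | 74% |
| 0.3 | 0.60 | 63% |
| 0.5 | 0.53 | 55% |
| 0.7 | 0.47 | 50% |

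The ρ = 0 row is the cost of losing four children at random. The rest of the drop is selection. With n alone changing, the gain detectable at 80% power goes from 0.66 SD (n = 20) to 0.75 SD (n = 16).

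**3. Exit test stands in for T2.** Let the exit test capture a fraction f of the child's final gain (A). The mean becomes 0.70 − 0.2·(1 − f)·m, where m is the mean final gain of the four who leave: m = (0.70 − 0.8 × mean of the 16)/0.2.
- ρ = 0.3: m = (0.70 − 0.48)/0.2 = 1.10. With f = 0.5, 0.70 − 0.11 = 0.59. With f = 0.75, 0.70 − 0.055 = 0.645, about 0.65.
- ρ = 0.7: m = (0.70 − 0.376)/0.2 = 1.62. With f = 0.5, 0.70 − 0.162 = 0.54. With f = 0.75, 0.70 − 0.081 = 0.62.

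Simulated power is about 79% to 75% for f = 0.5 and about 83% to 81% for f = 0.75, as ρ goes from 0.3 to 0.7.

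**4. Scheduled T2 kept for all.** The number stays at about 20 and the shift from this source is zero.

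**The case against.** A reader might infer that the plan simply discards the children for whom the method worked. The text does not support that.

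- Exit is a case-by-case decision, not automatic, and 5.3 asks for tests at that point. Outcome data may therefore exist, and step 3 shows that using them leaves much less damage than exclusion.
- Only children who reach re-enrolment can leave on this ground. Without a control group, their improvement cannot be equated with an effect of the method.
- Section 2.4 links early admission to a favourable start. Starting level is not gain, so ρ may be near zero, and then only numbers are lost.
- The two-in-ten rate comes from a retrospective series and need not carry over to this sample.
- A mixed model can use a child's T0 and T1 values, and 9.5 says that loss to follow-up must be weighed in interpretation.
- The protocol does separate research from care for family decisions.

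All of this stands and limits the size of the problem. None of it supplies a month-24 value or a rule for the exit test. The exclusion sentence in 9.5 can also be read as removing the T0 and T1 data that the mixed model would use.

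A reader might also infer that the final result must understate the gain. That does not follow either: exits for lasting aggravation, in the same section, and family withdrawals act in the other direction.

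**Conclusion.** The point holds in a limited form. As written, children who improve enough for re-enrolment may lack a scheduled T2 value because of their outcome, and the protocol neither keeps that assessment nor says how an exit test is used.

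If 4 of 20 exit and the true gain is 0.70 SD, exclusion gives a mean of 0.70 to 0.47 SD and power of about 74% to 50%, against 84% (ρ from 0 to 0.7). Substituting exit tests that capture half to three quarters of the final gain gives 0.65 to 0.54 SD and about 83% to 75% (ρ from 0.3 to 0.7). The exit rate, effect size, correlation and captured fraction are assumptions, so these are illustrations, not predictions.

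The existence of the gap is certain from the text; its size is not. This source of bias runs against the method, and the net direction over all kinds of exit is not fixed.

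**What to change.** - **5.3:** for the improvement case, separate the end of 3I care from the end of study follow-up. Keep the scheduled T1 and T2 assessments for these children as long as the parents agree.
- **9.1:** include them in the T2 versus T0 analysis whatever their care or school status, and report that status at month 24 beside the scores.
- **9.5:** extend the early-exit rule to improvement exits. State that an exit test is analysed at its actual time and does not replace T2. Keep the child's other available assessments in the mixed model, and name this direction of bias next to the one already given.

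Decisions about care or schooling are not touched, nor is the exit ground for undesirable effects.

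The cost is a short amendment, and the month-24 assessments are already planned for about 20 children. It should be made before children exit, because missed assessments cannot be recovered. One small downside is that the month-24 result then describes starting 3I, not 24 uninterrupted months of it.

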| **2** | **Scientific justification and general description of the research**  The 3I method (individual, intensive and interactive) is a method of developmental management of autism and pervasive developmental disorders, originally inspired by the program Son-Rise ®, developed by AEVE when The HAS (Haute Autorité de Santé: Health Hight Authority) in March 2012 ranked this method as a non-recommended method in the absence of expert consensus and scientific assessment. The HAS however expressed the wish, that innovative methods, namely the 3I method, be the subject of clinical evaluations.  The "medical device" to be evaluated consists of support of the child (or teenager) in a playroom taking into account the sensory particularities of the child to facilitate the possibility of an exchange. For the most part the support is done by nonprofessional volunteers. Volunteers are trained in the 3I method, both before the start of the care, and during monthly experience-sharing meetings, in the presence of parents, and a professional psychologist. – fully trained to the 3I method and approved by AEVE.  The play-therapy sessions, lasting one and a half hours, two in the morning and at least two in the afternoon, putting the child in contact with about thirty volunteers during the week. The sessions are child-friendly and non-directive, but the volunteers are aware of ongoing developments that they need to make. As for the therapy sessions of exchange and development (developed by [name] at the University Hospital of Tours), these are individual play sessions with the child in which the key words for the attitude of stakeholders are: "serenity, availability, reciprocity".  The support lasts two to three years and includes steps (or phases) described in the attached INPI Filing Brochure (AEVE1 DEC1 PJ1) |
| **2.1.a** | **The intended purpose of the medical device or in vitro diagnostic medical device, if applicable specified in the instruction leaflet or instructions for use, and that provided for research:** not applicable |

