| **2.1.b** | **Contraindications, possible risks:**  The implementation of the 3I method for eight years (applied to date by more than 300 children or adolescents) has not shown any contraindications or possible risks. The intensity does not relate to the course of each session, but to the fact that the level of interaction with the child remains the same throughout the day and that the schedule of the child does not involve a timeout. During Phase 1, the child spends the most time in the "playroom", one-and-a-half hour sessions will be held with a volunteer (preferably on the same day and at the same time each day of the week), two in the morning and two or three in the afternoon. During phases 2 and 3, the child's schedule will be more diversified and oriented more towards the discovery of the outside world, prior to collective schooling. |

| 2.1.c | **Preliminary safety and performance checks:**  The security of the playroom is the responsibility of the parents; the typical equipment of the playroom recommended by the 3I method does not present any risk of physical safety (see file AEVE1 DEC1 PJ2)  The risk of maltreatment, even acts of pedophilia, can not be completely excluded, but it is very limited by the permanent presence near the playroom of a person from the family circle, which welcomes the successive volunteers and can hear what's happening in the playroom; in addition, the sessions are filmed, and any interruption of a shooting would alert the parents. |
| --- | --- |
| 2.1.d | **Summary of Training Needed by volunteers:**  The nonprofessional volunteer must be be comfortable with children and not to feel like wasting time playing with a child. Training is provided in several stages; First presentation of the method is made to people who express their interest during a research campaign of "volunteers". Second, a training is provided to new participants to present the child and its characteristics and to give first advice on how to behave in a playroom. Continuous training is then provided each month (after 4 sessions for each participant in average, based on a weekly commitment) by a psychologist, who personally ensures a weekly play session. The sessions being filmed, the permanent formation can be based on concrete examples. |

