| **12** | **Ethical considerations**  Respect for the privacy of the families whose children will participate in the study is a key concern of the Promoter of this research.  The application for research authorization will be made to the CNIL under the responsibility of the Promoter.  To date, no data available suggests that children or adolescents participating in this research are associated with 3I management.  The realization of this research is an essential condition for improving the administrative and financial management of families choosing support 3I |
| **13** | **Processing and preservation of documents and research data**  All the files of the study will be archived for a period of 15 years, under the responsibility of the Promoter using, preferably and subject to the agreement of its director, the means that the laboratory of use of digital techniques de la Villette could put at his disposal.   The promoter of the study will subcontract, in the absence of agreement with the laboratory above, to an outside company, such as Archiveco, for a period of 15 years, the storage of the following documents:. - Protocol with annexes, amendments; - Consent Forms signed and initialed. - Information forms on experimentation. - Observation books (originals) with additional documents. - Follow-up document of the clinical study. - All administrative documents and correspondence related to the study. - Data acquired (test results) - Study report. |
| 14 | **Financing and insurance**  Funding for the pre-study was provided in 2013 by a grant from the Bettencourt Schueller Foundation.  AEVE had 45,000 euros in cash on 1 January 2014 (30,000 euros from the Bettencourt Schueller Foundation and 15,000 euros from the Deehcq Institut de France Foundation). The Bettencourt Schueller Foundation is also committed to pay a grant balance of € 10,000 for this project. The cost of the 2014 2016 project is estimated at € 70,000 and AEVE has sufficient capital to cover the unfinanced balance if no new grant is obtained.  AEVE will present a certificate of insurance covering his civil liability as a promoter as well as for the investigator, intervening free of charge, and the collaborator of the investigator, acting as a self-entrepreneur. |

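### The one adverse-event notification route that the protocol describes runs through the sponsor-approved psychologist who takes part in the care, and none is described for parents, so harms are at risk of under-reporting

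*Protocol*

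**What the plan says.** **Who notifies.** Protocol section 8 states that events or adverse effects, in the sense of section 5.3, "will be notified by the 3I psychologist assigned to the child to the investigator". No other notifier is named.

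**Who that person is.** Section 2 describes the psychologist as "fully trained to the 3I method and approved by AEVE". Section 14 identifies AEVE as the sponsor: "AEVE will present a certificate of insurance covering his civil liability as a promoter". Under section 2.1.d the volunteers' continuous training is given each month "by a psychologist, who personally ensures a weekly play session".

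**What parents are responsible for.** Section 8: "Child safety is ensured mainly by his parents". Section 2.1.c: "The security of the playroom is the responsibility of the parents". Section 8 also accepts that the risk of abuse by volunteers has to be taken seriously, and relies on someone near the playroom and on the filming to reduce it.

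**What is done with the information.** In section 5.3 the investigator and the collaborating investigator, "possibly solicited by a referent psychologist of the child, will decide on the premature exit of the study". Section 4.7 would stop the study if serious adverse effects led to discontinuation in one quarter of children, or if at least one third worsened at intermediate assessments.

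**The concern.** The person who must notify a harm helps to deliver the care, trains the volunteers who deliver most of it, and holds an approval granted by the sponsor. A report may therefore reflect on the notifier's own work or on people the notifier has trained. The parents are closest to the child and carry most of the safety role, but the protocol text gives them no described way to report directly to the investigator.

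Two things are at stake. The one-quarter rule in section 4.7 counts events for which section 8 is the only written notification route. And if few harms were reported among about 20 children, a reader could not tell a low harm rate from incomplete notification.

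**Working it through.** This is mainly a check of text against text. The protocol states no figure for harms or for their notification, so there is none to reproduce.

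**Step 1: other ways in which a harm could reach the study team.**

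| Channel | Where | Avoids the 3I psychologist? | Is it event reporting? |
|---|---|---|---|
| Notification by the 3I psychologist | Section 8 | No | Yes |
| Monthly meeting with parents | Section 2 | No | No, experience sharing |
| Volunteers' notes, with passages flagged for review | Section 4.5 | No, review is by the psychologist | No |
| Parents' questions to the investigator | Section 4.2 | Yes | No, stated where parents are informed of the study |
| CARS and VABS at T0, T1, T2; ADI-R at pre-inclusion and T2 | Sections 4.2, 7.2 | Yes | No, they measure severity, function and diagnostic domains |
| Testing after early termination | Section 9.5 | Yes | No, it estimates the child's evolution |

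The only row that is event reporting is also the one that depends on the psychologist.

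**Step 2: timing of the independent channel.** T0, T1 and T2 fall at about months 1, 12 and 24. The gaps are 12 − 1 = 11 months and 24 − 12 = 12 months. An event at month 3 could wait 12 − 3 = 9 months for the next scheduled interview, which has no stated adverse-event question.

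**Step 3: the stopping rules.** With about 20 children (section 9.2), one quarter is 20/4 = 5. One third is 20/3 = 6.7, so 7. The one-third rule uses assessment scores and does not need the psychologist's notification. The one-quarter rule counts serious adverse effects, for which section 8 is the only written notification route.

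**Step 4: sensitivity of the one-quarter rule (illustration only).** Let p be the true proportion of children with a qualifying harm and s the share of these that is notified. Both are assumptions. The number notified is taken as binomial with n = 20 and probability p × s, and the table gives P(X ≥ 5).

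| p | s = 1 | s = 0.8 | s = 0.5 |
|---|---|---|---|
| 0.25 | 0.59 | 0.37 | 0.10 |
| 0.30 | 0.76 | 0.54 | 0.17 |
| 0.40 | 0.95 | 0.82 | 0.37 |

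At p = 0.30 and s = 0.5, for example, p × s = 0.15 and P(X ≥ 5) = 0.17, against 0.76 with full notification. The count is sensitive to incomplete notification, but the table says nothing about how incomplete it would be.

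**The case against.** The strongest reply is that the study team is not blind to harm without the psychologist. The only undesirable effect that section 5.3 describes is a lasting aggravation of behavioural disorders, and parent interviews bear on behaviour and function. Worsening there feeds the one-third rule directly. A family's withdrawal is handled in sections 5.3 and 9.5, so a discontinuation would usually be seen even if its cause were not. Parents meet the psychologist monthly, sessions are filmed, and section 5.3 promises compliance with the regulation on undesirable effects.

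Much of this stands, and it rules out several stronger readings that a reader might infer:

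- *Harms reach the investigator only through the psychologist, or otherwise never.* The interviews and the one-third rule contradict this. Section 5.3 makes the psychologist's part in the exit decision optional, so it is no evidence of a sole channel.
- *The notifier sees only 4–5% of the care.* At 30 to 35 hours a week in 1.5-hour sessions there are 20 to 23.3 sessions, and one of them is 1/20 = 5.0% to 1/23.3 = 4.3%. That is personal presence at sessions. Notes, films and monthly meetings also inform the psychologist, so it does not measure awareness of events.
- *The protocol rejects any independent check of harms.* Section 11 says that the tests "did not seem to require the intervention of a third party in quality control and quality assurance", and its reason is their repetitive nature. That concerns test administration.
- *Parents have no route at all.* The information leaflet cited in section 4.2 is not shown and may carry a contact.
- *Under-reporting is likely.* No figure in the document supports more than a risk.

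The reply does not remove the point. Interviews 11 to 12 months apart are not event reporting, the monthly meeting passes through the same person, and the regulatory commitment comes without a procedure. Developmental scores are a poor means of detecting the abuse risk that section 8 itself raises.

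**Conclusion.** The point holds as a risk. Section 8 lays down one notification route, through a psychologist who is approved by the sponsor and partly responsible for the care, and the text at hand describes no direct route for parents. Harms, and the serious adverse effects counted towards 5 of 20 children in section 4.7, are at risk of under-reporting.

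The size cannot be derived from the document. The binomial figures show sensitivity under assumed rates, with independence between children. The conclusion also assumes that the leaflet, which is not shown, sets up no reporting route for parents. This is a cheap improvement to safety reporting and leaves the efficacy analysis unaffected.

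**What to change.** In section 8, name the parents as direct notifiers to the investigator, alongside the 3I psychologist, whose route stays. State the contact in the information leaflet if it is not already there.

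Have the evaluator put a short fixed set of adverse-event questions to the parents at each remaining scheduled interview (T0, T1, T2) and at any exit contact. The answers should go to the investigator independently of the 3I psychologist. Questions at pre-inclusion would give a baseline at most, so they are not needed for this purpose.

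Cost: a few minutes within interviews that already take about 2.5 hours per evaluation (CARS 1 h plus VABS 1.5 h, section 4.6), one form, and some duplicate reports to reconcile. Existing staff can do it. Limit: section 4.2 gives the study a retrospective part, and assessments already completed there cannot be covered prospectively.
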